Potential participants (identified through screening waiting lists by a researcher at each of our sites, or through direct referral from professionals or direct advertisement to patients) will be invited to a telephone eligibility screen. If a participant meets the eligibility screen the researcher will give further details of the trial, send information leaflets and a consent form by post and offer them a face to face appointment (either in the clinical site or the patients own home) within 7 days from the telephone screen. At the face to face interview consent and baseline measures will be taken. Follow up interviews at 3, 6 and 12 months may be carried out over the telephone or questionnaires completed and returned by post. This will be dependent on participant preference should they be unable to meet face-to-face.

To ensure the removal of selection bias allocation will be concealed from the researchers completing assessments by randomisation through a central randomisation service. Details of eligible consenting patients will be entered onto a secure web based system administered by the York Clinical Trials Unit, which will then provide the treatment allocation. The system will generate an automatic email to both the site lead and the mental health worker of the participant’s treatment allocation. We have used this method successfully in one completed trial [13] and an ongoing mental health RCT [REEACT: the Randomised Evaluation of the Effectiveness and Acceptability of Computerised Therapy; NIHR HTA, PI [name]]. Allocation will involve minimisation on four important factors: OCD severity (moderate/severe), anti-depressant medication (yes/no), depression (mild/moderate/severe) and chronicity (duration of OCD – 0—5 years/ 6-10 years/ 10 years and over), with the aim of ensuring a balance across treatment arms.

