**3.8 Proposed sample size:**

Three pair-wise comparisons are planned between (i) self-managed therapy packages (cCBT v bibliotherapy), (ii) CBT waiting list and cCBT (iii) CBT waiting list and bibliotherapy.

In trials of non-pharmacological interventions it is recommended that variation between care-providers is considered in sample size estimation and statistical analysis. In this trial there could be variation by therapist (mental health workers) in the two self-managed therapies. For the comparisons of CBT waiting list with cCBT or bibliotherapy we have assumed between therapist variation in the active treatment corresponding to a partially-nested design [17]. For the comparison of cCBT v bibliotherapy the same set of therapists will "supervise" both interventions so the trial is therefore a cross-design [17]. Sample size is estimated using the methods described by Walwyn & [name] [17].

We are not aware of directly relevant estimates for intra-cluster correlation coefficient (ICC) for therapist required for sample size for comparison (ii) & (iii) or the ICC between treatments within therapist for comparison (i). We expect the ICC between treatments within therapist to be less than half the ICC between therapists. With a total sample size of 432 clients and 24 therapist (average of 6 therapists per clinical site) each with a caseload of 6 cCBT and 6 bibliotherapy clients the trial will have a power greater than 80% to detect a difference of 3 YBOC points for each comparison provided the ICC for therapist does not exceed 0.06 and the ICC for treatment within therapist does not exceed 0.015. This calculation assumes a 85% follow-up rate to 6 months (87% was achieved within [name] et al [1]), a 1.67% significance level to maintain a 5% sig level for three pair-wise comparisons, SD for the primary outcome YBOC at 6 months of 7.3 unit, a correlation between baseline YBOCS and 6 month YBOC of 0.43 [1]. In the event that the ICC for therapist is less than 0.1 and the ICC for treatment within therapist is less than 0.05 (which would represent unexpectedly large values), the power is still greater than 75%. By virtue of involving a comparatively large number of therapists the trial is therefore robust again larger ICC values for therapist.

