**3.10 Statistical analysis:**

A full statistical analysis plan for the analysis of primary and secondary outcome measures including any sub-group analyses will be prepared and presented to the TSC (Trial Steering Committee) prior to the commencement of the trial analysis. During the recruitment and follow-up period regular reports will be prepared for the TSC/DMEC on data quality.

Statistical analysis of outcome will follow intention-to-treat principles: patients will be analysed according to randomised group and outcome data will be sought and included in the analysis for all patients irrespective of completion of treatment. Preliminary statistical analysis will model the pattern of missing data in terms of baseline characteristics of patients.

Statistical analyses of the primary outcome measure, YBOC at 3 months, will be based on a mixed model analysis with random effects for therapist and covariates including baseline YBOC and variables potentially predictive of outcome including minimisation variables. This will be used to compare all three arms. Conditional on significance at a 5% level, pairwise comparisons between arms will be carried out using a Bonferroni corrected p-value. Similar analyses will be carried out for quantitative secondary outcomes. A logistic mixed model will be use to compare the percentage of patients requiring full CBT between treatment adjusted for baseline severity.

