Differences in mean costs will be analysed using standard parametric t-tests with the validity of results confirmed using bias-corrected, non-parametric bootstrapping (repeat re-sampling) [40]. Despite the skewed nature of cost data, this approach is recommended to enable inferences to be made about the arithmetic mean [41].Tests will be adjusted for baseline cost, baseline YBOC score and variables potentially predictive of outcome including minimisation variables.

Cost-effectiveness will be explored in terms of incremental cost per quality adjusted life years; calculated using the EQ-5D measure of health related quality of life, and using rules of dominance and extended dominance for a three-arm comparison [42]. The primary perspective of the analysis will be the NHS/Personal Social Services perspective preferred by the National Institute of Health and Clinical Excellence. Secondary analyses will take a societal perspective. In line with the key objectives of the proposed trial, the following cost-effectiveness analyses will be undertaken:

1. Self-managed CBT (cCBT and bibliotherapy) compared to no active intervention (i.e. CBT waiting list) in the management of OCD patients in the short-term (3 or 6 month follow up, dependent on pilot phase results, as described above).
2. Self managed therapies plus usual care (waiting list plus access to therapist led full CBT) versus usual care alone at 12 month follow up.

Nonparametric bootstrapping from the costs and effectiveness data will be used to generate a joint distribution of incremental mean costs and effects for the three arms. This will then be used to calculate the probability that each of the treatments is the optimal choice, subject to a range of possible maximum values (ceiling ratio) that a decision maker might be willing to pay for a unit improvement in outcome. Cost-effectiveness acceptability curves are presented by plotting these probabilities for a range of possible values of the ceiling ratio [43]. These curves are a recommended decision-making approach to dealing with the uncertainty that exists around the estimates of expected costs and expected effects associated with the interventions under investigation [44]

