**3.12 Proposed outcome measures:**

The primary outcome will be OCD symptoms as measured by the Yale Brown Obsessive Compulsive Checklist YBOCS [12] observer-report version. Secondary outcomes will include self-reported health-related quality of life (SF-36), self-reported OCD symptoms (YBOCs self-rated), generic mental health (CORE-OM), depression (PHQ9), anxiety (GAD-7), functioning (WSA), health-related quality of life (EQ5D), employment status (IAPT Employment Status questions A13 –A15), patient satisfaction (CSQ) and acceptability (qualitative interviews), and % patients not improved or partially improved requiring more intensive CBT. Our primary outcome point (3 month follow up) will be determined by the pilot study. A 6 and 12 month follow up will also be included.

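### The logistic model for needing full CBT is adjusted for baseline severity alone, leaving out two or three of the four minimisation factors that the other analyses include; some power may be lost if those factors are prognostic

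*Protocol*

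**What the plan says.** Section 3.3.2 of the protocol sets the allocation rule: "Allocation will involve minimisation on four important factors: OCD severity (moderate/severe), anti-depressant medication (yes/no), depression (mild/moderate/severe) and chronicity", the last of these in three bands of illness duration.

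Section 3.10 gives the primary mixed model "covariates including baseline YBOC and variables potentially predictive of outcome including minimisation variables". It then says: "Similar analyses will be carried out for quantitative secondary outcomes". The binary outcome is handled separately: "A logistic mixed model will be use to compare the percentage of patients requiring full CBT between treatment adjusted for baseline severity". Section 3.12 lists the outcome as the percentage of "patients not improved or partially improved requiring more intensive CBT".

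Section 3.11 uses the wider rule for costs: "Tests will be adjusted for baseline cost, baseline YBOC score and variables potentially predictive of outcome including minimisation variables".

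**The concern.** Three of the four kinds of analysis (primary, quantitative secondary, costs) carry the minimisation variables. The fourth names a shorter list. The sentence extending the primary approach is limited to quantitative outcomes, so it does not reach the logistic model. The protocol therefore states a covariate rule for this outcome, and that rule differs from the one it uses elsewhere.

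Minimisation makes the arms more alike on its factors than simple randomisation would. If such a factor predicts outcome and is left out, the model-based standard error takes no credit for that balance and is too large for the true sampling variation. In a logistic model, the omission also pulls the treatment log-odds ratio towards zero. The result is a test that rejects less often than its nominal level and has less power.

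The outcome has some weight. Section 3.2 names as an evidence gap how many people will not improve with self-managed packages and will need more intensive CBT. Section 3.3.2 asks whether self-managed therapy reduces the need for conventional CBT. Section 3.8 justifies power for YBOCS only, so no stated power margin covers this comparison.

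**Working it through.** **Covariates side by side**

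| Analysis | Section | Minimisation variables included? |
|---|---|---|
| YBOCS at 3 months | 3.10 | Yes |
| Quantitative secondary outcomes | 3.10 | Yes, by similarity to the primary |
| Costs | 3.11 | Yes |
| Needing full CBT (logistic) | 3.10 | Baseline severity only |

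**The plan's own power figure.** The protocol gives no power or event rate for the binary outcome. Its only power statement is above 80% for YBOCS (section 3.8: "With a total sample size of 432 clients and 24 therapist", 85% follow-up, 1.67% level, SD 7.3, correlation 0.43, difference 3, therapist ICC 0.06). It reproduces:
- Evaluable per arm: 144 × 0.85 = 122.4, and per therapist and arm 6 × 0.85 = 5.1.
- Adjusted SD: 7.3 × √(1 − 0.43²) = 6.59.
- Partially nested variance: 6.59²/122.4 × (2 + 4.1 × 0.06) = 0.797, so SE = 0.893.
- Power: Φ(3/0.893 − 2.394) = Φ(0.966), about 83%.

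This confirms the design inputs but says nothing about the logistic model.

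**Simulation of the logistic test**

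From the protocol: 432 patients, three arms, four minimisation factors with 2, 2, 3 and 3 levels, 85% follow-up, and 5% and 1.67% levels (taken as two-sided).

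Assumed, because the protocol does not give them:
- 85% of allocations made by minimisation and 15% at random;
- equally frequent levels of antidepressant use, depression and chronicity;
- log-odds of 0.5 per SD of baseline YBOCS;
- a common odds ratio (OR) per level for the three other factors;
- a treatment OR of 1/2.3 = 0.43 under the alternative;
- no therapist effect.

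The statistic is the Wald test of one active arm against waiting list. Severity only means baseline YBOCS. The full model adds antidepressant use (1 parameter), depression (2) and chronicity (2). There were 2,500 runs under the null and 1,500 under the alternative.

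| OR per level of omitted factors | Type I error at 5%: severity only / full | Empirical/model SE, severity only (null) | Power at 5%: severity only / full | Power at 1.67%: severity only / full |
|---|---|---|---|---|
| 1.0 | 5.2% / 5.5% | 1.01 | 88.5% / 88.5% | 78.3% / 79.0% |
| 1.5 | 4.3% / 5.3% | 0.99 | 84.9% / 86.4% | 72.3% / 74.8% |
| 2.0 | 3.6% / 4.6% | 0.95 | 80.5% / 84.8% | 65.9% / 72.8% |
| 3.0 | 2.6% / 5.3% | 0.90 | 66.5% / 78.7% | 47.9% / 63.3% |

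Power lost at 5%: 0, 1.5, 4.3 and 12.2 points. Power lost at 1.67%: 0.7, 2.5, 6.9 and 15.4 points. Over ORs of 1.5 to 2 that is roughly 1 to 7 points.

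The Monte Carlo standard error of a 5% rejection rate is √(0.05 × 0.95/2,500) = 0.44 points. The shortfall at OR 1.5 (4.3%) is therefore within simulation noise of 5%, while those at 2 and 3 are not.

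Attenuation also shows. Against a true log-odds ratio of −ln 2.3 = −0.83, the severity-only mean estimate is −0.80 at OR 1.5 and −0.73 at OR 2. The full model gives −0.86 at both.

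**Second simulation.** A separate two-arm run used 122 per arm, 90% biased allocation, a 5% test, a treatment log-odds ratio of −0.9 and no therapist effect. At log-odds of 0.5 and 0.8 per factor level (ORs 1.65 and 2.23), type I error was 3.8% and 3.4% with severity only, against 5.2% with all four factors. Power was 89.2% against 91.4%, and 82.1% against 87.9%: losses of 2.2 and 5.8 points. Direction and size agree.

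**The case against.** **The covariate list for a secondary outcome belongs in the SAP.** Section 3.10 promises a full SAP, and a protocol silent on these covariates would not be at fault. This one is not silent. It states a rule, so a SAP that follows it carries the omission forward and a SAP that widens it departs from the protocol. The objection lowers the importance of the point but does not remove it.

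**The wording may not be exclusive.** The sentence does not say that only severity is used, and baseline severity is undefined. Depression is also graded by severity in the minimisation. A reader might infer that three of the four factors are certainly omitted. The text supports only two or three.

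**A short list may be deliberate.** Section 3.3.2 reports that most pilot patients had started CBT by 6 months. If the outcome is counted by CBT uptake at that point, one category could be small, and extra parameters alongside random effects could strain the model. This stands as a reason for a reduced form. It does not justify leaving the factors out, and the protocol does not offer it as a reason.

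**The size is assumed.** This stands. Nothing in the protocol says how strongly antidepressant use, depression or chronicity predict needing full CBT. Losses of 12 to 15 points require an OR of 3 per level for all three factors at once.

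**Comparability of odds ratios.** A reader might infer that the odds ratio fails to match the other analyses. Those analyses estimate mean differences, so there is no other odds ratio to match.

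**Conclusion.** The difference in covariate rule is in the text and is unexplained. Its consequence is conditional. If the omitted factors do not predict the outcome, the test has its nominal size and virtually no power is lost. If they do, as the protocol allows by grouping the minimisation variables with potentially predictive ones, the test is somewhat conservative. It then loses roughly 1 to 7 points of power at assumed ORs of 1.5 to 2 per level. Including the factors brings the size back to about 5%.

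These figures rest on the assumed event rate, factor distributions, treatment effect and allocation probability, and on ignoring the therapist effect that the mixed model would carry.

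A reader might infer that the test necessarily loses power, or that it is invalid. The documents support neither. The loss depends on prognostic strengths they do not give, and false positives are not inflated. The primary outcome and the sample size are untouched. This is a minor point on one secondary outcome.

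**What to change.** Reword the last sentence of section 3.10 so that the logistic mixed model adjusts for baseline YBOCS and the minimisation variables (OCD severity, antidepressant medication, depression, chronicity), as in the primary analysis. If the shorter list is intended, say so, give the reason, and define baseline severity.

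The factors are already recorded, since allocation needs them. The cost is one sentence and up to about five parameters: 1 for antidepressant use, 2 for depression and 2 for chronicity. Entering the severity band beside continuous YBOCS would add one more.

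To guard against a sparse outcome category, pre-specify a reduced form, for example depression and chronicity as linear scores, which cuts the five parameters to three. Fix it before analysis, so that the covariate choice cannot depend on the results.

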**3.11 Economic analysis:**

Little evidence exists regarding the service use or costs associated with OCD, or the cost-effectiveness of alternative treatment strategies [22-24], with the exception of a small number of cost of illness or costing studies [25-28], productivity loss [27] and caregiver burden [29] estimates. Clinical evaluations of treatment alternatives for OCD that have included a cost or cost-effectiveness component have been severely limited to the cost of the interventions under evaluation, with no data collected on the impact of the treatment options on the use of other health and social services, patient and family costs or productivity losses [11,30,31]

The proposed economic evaluation will take a societal perspective. Data will be collected on the use of all hospital and community health and social services, productivity losses and costs to patients/families. To the best of our knowledge, no OCD specific tool for measuring use of services and other resources exists. Instead, the Adult Service Use Schedule (AD-SUS), a generic measure developed by the applicants (SB) and successfully applied to a range of studies of adult mental health services [32-34] will be adapted to ensure it adequately captures resources appropriate to OCD. The AD-SUS will initially be adapted for OCD through review of relevant literature and discussions with the clinical team. The adapted version will then be tested at baseline interview with participants in the pilot phase to ensure all important resources are captured. Intervention resources will be collected from therapist records to ensure accuracy and avoid unblinding research assessors.

The unit cost of study interventions will be calculated directly using established methods of micro-costing [35]. Calculations will require data on therapist salaries, including appropriate overheads and employers’ oncosts (national insurance and superannuation), working time and estimates of the ratio of direct face-to-face to indirect time. The cost of cCBT will require information on the licensing costs, plus data on any additional purchases of equipment required. For all other health and social services, nationally applicable unit costs will be applied [36-38]. Productivity losses will be calculated using the human capital approach, which involves multiplying days off work due to illness by the individual’s salary [39]

Differences in mean costs will be analysed using standard parametric t-tests with the validity of results confirmed using bias-corrected, non-parametric bootstrapping (repeat re-sampling) [40]. Despite the skewed nature of cost data, this approach is recommended to enable inferences to be made about the arithmetic mean [41].Tests will be adjusted for baseline cost, baseline YBOC score and variables potentially predictive of outcome including minimisation variables.

Cost-effectiveness will be explored in terms of incremental cost per quality adjusted life years; calculated using the EQ-5D measure of health related quality of life, and using rules of dominance and extended dominance for a three-arm comparison [42]. The primary perspective of the analysis will be the NHS/Personal Social Services perspective preferred by the National Institute of Health and Clinical Excellence. Secondary analyses will take a societal perspective. In line with the key objectives of the proposed trial, the following cost-effectiveness analyses will be undertaken:

1. Self-managed CBT (cCBT and bibliotherapy) compared to no active intervention (i.e. CBT waiting list) in the management of OCD patients in the short-term (3 or 6 month follow up, dependent on pilot phase results, as described above).
2. Self managed therapies plus usual care (waiting list plus access to therapist led full CBT) versus usual care alone at 12 month follow up.

Nonparametric bootstrapping from the costs and effectiveness data will be used to generate a joint distribution of incremental mean costs and effects for the three arms. This will then be used to calculate the probability that each of the treatments is the optimal choice, subject to a range of possible maximum values (ceiling ratio) that a decision maker might be willing to pay for a unit improvement in outcome. Cost-effectiveness acceptability curves are presented by plotting these probabilities for a range of possible values of the ceiling ratio [43]. These curves are a recommended decision-making approach to dealing with the uncertainty that exists around the estimates of expected costs and expected effects associated with the interventions under investigation [44]

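### Section 3.11 names t-tests and bootstrapping with no allowance for therapist clustering, so uncertainty in the waiting-list cost-effectiveness contrasts is likely to be modestly understated

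*Protocol*

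**What the plan says.** On costs, protocol section 3.11 states: "Differences in mean costs will be analysed using standard parametric t-tests". A bias-corrected bootstrap is to confirm the validity of those results. On covariates: "Tests will be adjusted for baseline cost, baseline YBOC score and variables potentially predictive of outcome including minimisation variables". On the cost-effectiveness plane and acceptability curves: "Nonparametric bootstrapping from the costs and effectiveness data will be used to generate a joint distribution of incremental mean costs and effects", for all three arms. The section names no therapist term, does not give the resampling unit of either bootstrap, and does not say how QALYs are adjusted.

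Elsewhere the protocol takes therapist variation seriously. Section 3.8 says that "it is recommended that variation between care-providers is considered in sample size estimation and statistical analysis". It treats each comparison with the waiting list as partially nested, and cCBT against bibliotherapy as crossed, because the same therapists support both packages. Section 3.10 fits a mixed model with therapist random effects to YBOCS and promises the same approach for the other quantitative outcomes. EQ-5D is one of these (sections 3.3.2 and 3.12).

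**The concern.** The trial has one design and two standards for it. EQ-5D analysed as a clinical outcome gets therapist random effects. The same EQ-5D data, turned into QALYs and combined with costs, get no therapist term. A standard t-test assumes independent observations, and an ordinary bootstrap of individual patients shares that assumption, so it could not reveal the problem as a check on the t-test.

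Clustering in cost is plausible. Support contacts are part of the cost, and their number can vary in bibliotherapy, where section 3.4 sets a maximum for the brief sessions. Cost-effectiveness stands beside clinical effectiveness in the objectives (sections 3.1 and 3.3.2), and the acceptability curves are its main statement of uncertainty. If outcomes cluster by therapist in the active arms and this is ignored, standard errors against the waiting list are too small and the curves too steep.

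**Working it through.** **Inputs from section 3.8.** "With a total sample size of 432 clients" in three arms gives 432/3 = 144 per arm. There are 24 therapists, "each with a caseload of 6 cCBT and 6 bibliotherapy clients". Follow-up of 85% leaves n = 144 × 0.85 = 122.4 per arm and m = 6 × 0.85 = 5.1 patients per therapist per active arm. The SD is 7.3 and the correlation with baseline 0.43. The test level is "a 1.67% significance level to maintain a 5% sig level for three pair-wise comparisons", taken as two-sided. The pairs of ICCs (therapist; treatment within therapist) are 0.06 and 0.015, with an upper scenario of 0.10 and 0.05.

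**The plan's own figure.** The protocol claims "power greater than 80% to detect a difference of 3 YBOC points for each comparison" at the first pair, and more than 75% at the second.

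- Residual SD = 7.3 × √(1 − 0.43²) = 6.59.
- Variance of an active-minus-waiting-list difference = (6.59²/122.4) × [1 + (1 + 4.1 × ICC)].
- Power = Φ(3/SE − 2.39).

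| ICC | Power, this formula | Range over variants of the partially nested variance |
|---|---|---|
| 0 | 87.9% | – |
| 0.06 | 83.3% | 81–83% |
| 0.10 | 80.3% | 76–80% |

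The crossed comparison gives 82–88% at the first pair and 80–84% at the second. Both claims reproduce, so the design model is understood correctly. No figure is stated for the economic analysis.

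**Waiting-list contrasts for costs and QALYs.** The ICCs for YBOCS are borrowed here. The ratio of the correct to the unclustered standard error is √[(2 + 4.1 × ICC)/2]. The true size of a nominal 5% test is 2 × [1 − Φ(1.96/ratio)]. Treating incremental net benefit as approximately normal with the same ICC, a stated two-arm probability of 0.95 becomes Φ(1.645/ratio).

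| ICC | SE ratio | True size | 0.95 becomes |
|---|---|---|---|
| 0.01 | √1.0205 = 1.010 | 5.2% | 0.948 |
| 0.03 | √1.0615 = 1.030 | 5.7% | 0.945 |
| 0.06 | √1.123 = 1.060 | 6.4% | 0.940 |
| 0.10 | √1.205 = 1.098 | 7.4% | 0.933 |

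**cCBT against bibliotherapy.** A therapist effect common to both packages cancels from the difference. The remainder depends on what the second ICC means, which the protocol does not define in full. At 0.06 and 0.015 the SE ratio is:

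- √(1 + 4.1 × 0.06 − 5.1 × 0.015) = 1.08, if it is the correlation between patients of one therapist on different packages;
- √(1 + 4.1 × 0.015) = 1.03, if it is a therapist-by-treatment component;
- √(1 − 0.06 + 4.1 × 0.015) = 1.00, if it is such a component and the common therapist variance is also removed.

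At 0.10 and 0.05 the three readings give 1.07, 1.10 and 1.05.

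**Baseline EQ-5D.** The protocol gives no utility SD or correlation. Assume an SD of 0.20 to 0.30, correlations of 0.4 to 0.7 between visits, and a 12-month QALY as area under the curve through 0, 3, 6 and 12 months.

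- A chance baseline difference of one standard error is SD × √(2/122.4) = 0.026 to 0.038.
- The visit weights are 0.125, 0.25, 0.375 and 0.25. At correlation ρ the QALY variance, in units of SD², is 0.28125(1 − ρ) + ρ, and its covariance with baseline is 0.125 + 0.875ρ.
- At ρ = 0.4 the unadjusted-to-adjusted SE ratio is √[0.569/(0.569 − 0.475²)] = 1.29. At ρ = 0.7 it is √[0.784/(0.784 − 0.7375²)] = 1.81.

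**The case against.** The strongest reply is that the effect is small. With 24 therapists and about five analysed patients each per arm, moving 0.95 to 0.94 or 0.93 is unlikely to change how a curve is read. Much of total cost arises outside the trial support sessions (other health and social services and, by 12 months, therapist-led CBT), which could dilute any therapist correlation. Both points stand and limit the size of the finding. They do not remove the inconsistency, because section 3.11 names a method and does not defer it.

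Several stronger readings are tempting, and the documents do not support them.

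- A reader might infer that QALYs will not be adjusted for baseline utility. Section 3.11 is silent on this: its covariate list follows the cost tests and is open-ended, so baseline EQ-5D is neither named nor excluded. Such detail is commonly left to an analysis plan.
- A reader might add that leaving it out makes the probabilities overconfident. It would not. It would lose precision and leave the estimate exposed to chance imbalance.
- A reader might take patient-level resampling as stated. It is an inference, since no resampling unit is given.
- A reader might call an adjusted t-test a contradiction. The text says that the tests will be adjusted, which can be read as a regression in which the arm coefficient is tested. This is loose wording.
- A reader might assume a much higher ICC for cost. A value of 0.20 would give a ratio of √1.41 = 1.19, but it has no source in the protocol and is twice the protocol's own upper scenario.

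**Conclusion.** The point holds as an internal inconsistency of modest size. Sections 3.8 and 3.10 require and apply an allowance for therapist variation; section 3.11 names methods without one. Followed in their ordinary form, those methods give standard errors that should be about 6% to 10% larger for each active arm against the waiting list.

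This rests on three assumptions: costs and QALYs have therapist ICCs of 0.06 to 0.10, like those assumed for YBOCS; the bootstrap resamples patients individually; and net benefit is approximately normal. At ICCs of 0.01 to 0.03 the shortfall is only 1% to 3%. For cCBT against bibliotherapy the effect may be nil at the protocol's main ICC values, and how large it could be turns on the meaning of the second ICC. Baseline EQ-5D is a matter for clarification only.

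**What to change.** In section 3.11:

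1. Replace the t-tests with regression for costs and for QALYs, using the covariates already listed and therapist random effects in the active arms only, with none in the waiting list.
2. Build the cost-effectiveness plane and acceptability curves from a bootstrap of the adjusted estimates. Resample therapists jointly across the two active arms, so that a drawn therapist brings both cCBT and bibliotherapy patients and the crossed structure is kept. Resample individual patients in the waiting list.
3. As a secondary clarification, name baseline EQ-5D utility as a covariate for QALYs, for precision and protection against chance imbalance.

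Intervention resources already come from therapist records, so the therapist should be identifiable. The cost is a change of wording, a little more programming and slightly wider intervals for the waiting-list contrasts. If baseline utility would not otherwise have been included, the third step should narrow the QALY intervals.
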